## Abstract

**Background:**

In routine psychiatric treatment most clinicians inquire about indicators of suicide risk, but once the risk is assessed not many clinicians systematically focus on suicidal thoughts. This may reflect a commonly held opinion that once the depressive or anxious symptoms are effectively treated the suicidal symptoms will wane. Consequently, many clients with suicidal thoughts do not receive systematic treatment of their suicidal thinking. There are many indications that specific attention to suicidal thinking is necessary to effectively decrease the intensity and recurrence of suicidal thinking. We therefore developed a group training for patients with suicidal thoughts that is easy to apply in clinical settings as an addition to regular treatment and that explicitly focuses on suicidal thinking. We hypothesize that such an additional training will decrease the frequency and intensity of suicidal thinking.

We based the training on cognitive behavioural approaches of hopelessness, worrying, and future perspectives, given the theories of Beck, McLeod and others, concerning the lack of positive expectations characteristic for many suicidal patients. In collaboration with each participant in the training individual positive future possibilities and goals were challenged.

**Methods/Design:**

We evaluate the effects of our program on suicide ideation (primary outcome measure). The study is conducted in a regular treatment setting with regular inpatients and outpatients representative for Dutch psychiatric treatment settings. The design is a RCT with two arms: TAU (Treatment as Usual) versus TAU plus the training. Follow up measurements are taken 12 months after the first assessment.

**Discussion:**

There is a need for research on the effectiveness of interventions in suicidology, especially RCT's. In our treatment program we combine aspects and interventions that have been proven to be useful in the treatment of suicidal thinking and behavior.

**Trial registration:**

ISRCTN56421759

## Background

Suicide has a low prevalence in the general population, but suicide ideation is remarkably common [1]. In The Netherlands about 10% of the general public reported that they ever had suicidal thoughts [2], and Casey et al. [3] found no differences amongst several European countries. When these patients enter treatment, they are confronted with a commonly held misconception amongst health care workers that suicidal thinking and behavior will vanish when underlying psychiatric problems are treated. We have very good reasons to believe this is not the case. Suicidal thinking fluctuates over time [4,5], and reoccurs in the majority of depressed individuals in a consecutive episode [6]. In a study amongst formerly suicidal patients, Williams et al. [7] showed that problem-solving abilities and autobiographical memory specificity, commonly associated with suicidal thinking and behavior, deteriorate when the patient's mood lowers again. Suicidality appears to become a syndrome irrespective of underlying psychiatric morbidity [8]. This is a reason for Oquendo et al. [9] to plea for a separate diagnostic category in the forthcoming DSM classification manual. A distinct psychiatric problem, which needs a specific intervention.

Clinicians in psychiatry are increasingly aware of the need for systematically assessing suicidal risk, but they lack the tools for addressing suicidal thinking as a specific goal in treatment. There is a shortage of well described, evidence based treatment methods for suicidal behavior and suicide ideation. A few randomized clinical trials focussing on self harm and suicidal behaviour have been published, like MACT [10] (Manual Assisted Cognitive- Behavior Therapy) and the study on cognitive therapy for suicide attempters by Brown et al. [11]. There are studies on suicidality as a component of treatment programs for borderline patients, like Dialectical Behavioral Therapy [12,13], Schema Focussed Therapy [14], and Mentalization Based Treatment [15]. Most of these interventions have been applied in the Netherlands, but they all are developed for specialized settings and specific patient groups. A reason for us to develop an intervention for a broad group of patients with suicidal thoughts. This new intervention should be easy to implement as an add on intervention. Therefore, it should not require highly specialized therapists.

The most consistent and convincing theories on suicidal thinking and behavior include hopelessness, so this should be the core component of our intervention. According to Beck [16] three variables constitute the so called negative triad: hopelessness, self-esteem and a negative perception of the environment. Hopelessness is considered to be the best predictor or indicator of the risk of suicidal behaviour [17]. Research shows that especially lack of positive future expectancies, as a part of hopelessness, is an important factor in developing suicidal ideations and behavior [18]. MacLeod et al. [19] have shown that specifically a deficit of positive anticipation about the future relates to hopelessness and discriminates between parasuicidal and non-parasuicidal groups. Parasuicidal patients show an absence of anticipation of pleasurable future events, but not an increased anticipation of unpleasant events [20]. Lack of positivity seems to be related to cluster B disorders, especially borderline and dissocial personality disorder [21]. MacLeod hypothesized that this shortage of positivity might reflect a lack of available sources or rewarding and enjoyable experiences, a cognitive inaccessibility of representations of future positive outcomes or it may represent an inability to derive pleasure from what are normally enjoyable events [22]. Research among older individuals by Hirsch et al. [23] reveals that positive future orientation is associated with less current and less worst point suicide ideation. These authors regret that no cognitive based treatment has focused specifically on enhancing future orientation.

Another element of any new intervention for suicidal individuals should be problem solving. According to Hawton et al. [24] forms of problem solving therapy are promising in the treatment of suicidal patients. Recent research by Eskin et al. [25] showed significant decrease of suicide risk when adolescents and young adults received PST. Consistent evidence has shown that people who attempt suicide have poor problem solving skills [26,27] and problem solving therapy showed to reduce levels of depression and hopelessness in patients who have attempted suicide [28]. A study among suicide attempters by Jollant et al. [29] shows that decision making is impaired in this group, evaluated in a period in which the participants had no axis I disorder. Several attempts have been made to influence problem-solving skills, like MACT [30], STEPPS [31] (Systems Training for Emotional Predictability and Problem Solving, and BATD [32] (Behavioral Activation Treatment for Depression). In general health practice Problem Solving Therapy (PST), developed by Nezu, Nezu and Perri [33], has proven to be helpful and it is one of the treatment methods in the Dutch Multidisciplinary Treatment Guidelines for Depression [34].

Some other available interventions have a stronger focus on dysfunctional cognitions, like the time-limited approach by Rudd, Joiner & Rehad [35], and cognitive therapy for suicide attempters, evaluated in a RCT by Brown et al. [36]. These authors developed a 10 week program in which they combined basic cognitive therapy with elements like safety seeking and behavioral experiments. They found a 50% lower reattempt rate in their cognitive therapy sample, even after 18 months.

Suicidal behavior is characterized by isolation and social detachment [37]. As a result local and governmental incentives to encourage health-seeking behavior and to increase social support were developed. Examples are the Scottish 'Choose Life' program, and Australia's 'Social Inclusion Suicide Prevention Initiative'. On a smaller scale we encourage the participants in our project to seek for a coach or buddy to support them during the training. We stimulate patients to involve partners or friends. We are working on a pool of volunteers that can be contacted when participants have no one who can act as their personal coach. This supportive role is an element in other programs as well, like in the Community Reinforcement Approach [38].

This led to the cornerstones that we used to develop an intervention which we called Future Oriented Group Training. The training addresses hopelessness and lack of future thinking, and includes elements from cognitive therapy and problem solving therapy. Furthermore, a main goal is to break through the social isolation most participants got stuck in. In this article we describe the outlines of the training and our research project.

## Methods/Design

### Design

In order to evaluate the effectiveness of our intervention program we carry out a pragmatic randomized clinical trial (RCT). The participants are randomly assigned to either treatment as usual (TAU), or treatment as usual plus our additional treatment (TAU+). There are three assessments: when participants enter the project (pre-measurement), after three month (post measurement), and the follow up measurement carried out one year after the baseline measurement.

This research has been approved by the METiGG, the medical-ethical committee for research in mental health care settings in the Netherlands.

### Participants

People enter this project in several ways. The main stream of participants (aged 18-65 years) enters the project after an initial assessment in two psychiatric hospitals in The Netherlands, both in-patients and outpatients. A smaller sample is recruited from the existing pool of patients already in treatment and who were referred to the program due to suicide ideation.

The intervention is open for patients with suicidal ideation, irrespective of comorbid psychiatric disorders. Patients in an acute manic or psychotic state and those who seek treatment primarily because of drugs problems are excluded. Suicidal behavior is not a reason to exclude patients. Participants are required to speak and read Dutch sufficiently to take part in the study. All participants signed an informed consent form.

### Randomization

The randomization is conducted by an independent statistician. The researchers receive the outcome of the randomization by email and schedule the participants accordingly.

### Sample Size

The effect size deemed worthwhile to be detected by the study is *d *= 0.5. This is what is generally judged to be a clinically relevant effect size [39]. Power calculations are based upon a type I error α = 0.05, a power of 0.80, and an effect size of 0.5, imply a minimum of 63 participants in the groups. We calculated power to be sufficient for both intention-to-treat and completers analysis. Expecting that 80% of the patients in the 'suicide ideations group' are willing to participate (before randomization), and a drop out of 20% after randomization, we need to include 75 patients in each of the two groups to maintain 63 completers.

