#### Analyses

We are particularly interested in the effect (Cohen's *d*) on the main parameter suicide ideation. The effectiveness analyses will be conducted according to both intention-to-treat (ITT) and treatment completers principles. In the ITT analysis all randomized participants in the treatment group are included, irrespective of adherence, actual treatment received, or withdrawal from treatment or assessment. The completers analysis will focus on those participants who took part in 80% or more of the sessions and completed the post measurement.

Descriptive and mediating variables will be analyzed in order to reveal variables that need to be taken into account as covariates in the primary analyses of treatment effects. In order to find differences between the effects of our Future Oriented Group Training and treatment as usual we will perform analyses of repeated measures. We expect data loss due to drop out of participants. By using latent random effects variables for each participant multi level multivariable analysis permits estimation of changes in repeated measures, even when not all post assessment data are available due to missing data.

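### 75 randomised per group with 20% drop-out leaves 60 completers, not 63, so the completers analysis falls slightly short of the stated 80% power

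*Protocol article*

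**What the plan says.** All the figures stand in one paragraph of the protocol article, Methods/Design, Sample Size. The requirement is derived first: "Power calculations are based upon a type I error α = 0.05, a power of 0.80, and an effect size of 0.5", which are said to "imply a minimum of 63 participants in the groups". The paragraph then claims: "We calculated power to be sufficient for both intention-to-treat and completers analysis". Next come two attrition figures: 80% of eligible patients are expected to agree to take part, a step placed explicitly before randomisation, "and a drop out of 20% after randomization". The conclusion drawn is that "we need to include 75 patients in each of the two groups to maintain 63 completers".

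The Analyses section defines completers as participants who "took part in 80% or more of the sessions and completed the post measurement", and defines the intention-to-treat analysis as including randomised participants whatever their adherence or withdrawal. No other part of the article gives a different drop-out rate or sample size.

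**The concern.** The number randomised, the loss rate and the number of completers are tied by a single multiplication, and the three stated values do not satisfy it. One of them must be wrong.

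The plan presents 63 as a minimum and 75 as the number that secures it, and on that basis claims adequate power for two analyses. If 75 per group does not secure 63 completers at the stated loss, the claim fails for the completers analysis on the plan's own inputs. A reader of the trial would then credit that analysis with slightly more power than the design gives it.

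**Working it through.** **Inputs, all from Sample Size:** alpha 0.05, power 0.80, d = 0.5, 20% drop-out after randomisation, 75 per group, 63 completers. Sidedness is not stated.

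**Step 1: reproduce the 63.** For a two-group comparison of means, n per group = 2(z₁₋α/₂ + z₁₋β)²/d².
- Two-sided: 2 × (1.960 + 0.842)²/0.25 = 62.8, so 63. This matches.
- The two-sided t-test gives 63.8, so 64, one patient more.
- One-sided versions give 50 (normal) or 51 (t-test) and do not match.

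The 63 is therefore sound as a two-sided normal-approximation figure, and two-sided testing is used below.

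**Step 2: apply the drop-out.**
- Completers from 75: 75 × (1 − 0.20) = 60, which is 3 short of 63.
- Number needed for 63: 63/(1 − 0.20) = 78.75, so 79 per group, or 158 in total against the planned 150.
- Loss at which 75 leaves 63: 1 − 63/75 = 16%, a rate that appears nowhere in the article.
- Multiplying instead of dividing gives 63 × 1.20 = 75.6, which is close to the stated 75. This may be where the figure came from, but the article does not show the step.

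**Step 3: the willingness rate.** It acts before randomisation. It governs how many patients must be approached (for 150 randomised, 150/0.80 = 187.5, so 188) and cannot change how many of those randomised complete.

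**Step 4: power at d = 0.5, two-sided alpha 0.05.** The normal approximation is Φ(d√(n/2) − 1.960). For n = 60 this is Φ(0.5 × √30 − 1.960) = Φ(0.779) = 78.2%.

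| n per group | Normal | t-test |
|---|---|---|
| 60 (completers left from 75) | 78.2% | 77.5% |
| 63 (stated minimum) | 80.1% | 79.5% |
| 75 (all randomised) | 86.5% | 86.0% |

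With 60 per group, the d detectable with 80% power is about 0.52 (t-test).

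**The case against.** The strongest reply is that the error hardly matters. By the approximation that yields 63, power at 60 is 1.8 points below 80%. By t-test it is 2.0 points below the value at 63 and 2.5 points below 80%. The detectable effect moves only from 0.50 to about 0.52. The intention-to-treat analysis is untouched if all 75 per group contribute. The planned repeated-measures model might also gain precision, although the article gives no correlation from which to size that gain and does not base its sample size on it. The argument about size stands and limits the weight of the point. It does not remove the contradiction.

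A second reply is that loss need not be equal in the two arms, since attendance at training sessions can be required only of the training arm. If 60 remained in one arm and all 75 in the other, t-test power would be 81.8%. But the plan states a single 20% rate without distinguishing arms, and 63 would still not be the number left in the arm with the loss.

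A reader might be tempted by four stronger readings. The article does not support them.
- *One effect size cannot serve both analyses, because non-attenders dilute the effect.* The article presents d = 0.5 as the difference worth detecting, not as a prediction for completers. A target of this kind can be applied to both analyses. If 0.5 were the intention-to-treat effect and the 20% lost gained nothing, the completers' effect would be 0.5/0.8 = 0.625, with about 92% power at 60 per group.
- *The 75 is counted before consent, so far fewer remain.* The 75 are placed in each of the two groups, and groups exist only after randomisation.
- *The 63 is itself wrong because a t-test needs 64.* That is a one-patient difference between two accepted methods.
- *The completer definition is stricter than the drop-out allowed for.* The article ties its 20% directly to completers and gives drop-out no separate definition, so this cannot be established.

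**Conclusion.** The sentence is wrong as written: 75 per group, 20% loss and 63 completers cannot all be true. On the stated loss the plan yields 60 completers per group, with 77.5% (t-test) to 78.2% (normal) power instead of 80%. The claim of sufficient power therefore fails, narrowly, for the completers analysis. It holds for the intention-to-treat analysis at about 86%. It would go too far to call the trial underpowered on this ground; the point is a minor to moderate correction.

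The figures assume a two-sided test, equal loss in both arms and a simple comparison of two means. The 86% further assumes that all 75 per group enter the analysis.

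**What to change.** Rewrite the last part of the Sample Size section so that its figures agree:
- State that 75 randomised per group with 20% drop-out yields 60 completers per group and about 78% power for the completers analysis at d = 0.5 (detectable d about 0.52).
- Confine the statement of sufficient power to the intention-to-treat analysis, with about 86% power at 75 per group.
- Give 79 per group as the number that would be consistent with 63 completers.
- Say that the 80% willingness rate sets the number of patients approached, and that the test is two-sided if that is so.

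The cost is a text correction and a slightly less favourable power figure for one analysis. No extra patients are needed if the figures are restated. Holding to 63 completers instead would mean 4 more per group, 8 in total.

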### Blinding

Given the nature of the intervention, it was impossible to blind the patients and the trainers as to which condition they participated in. The outcomes will be assessed by blinded interviewers.

### Experimental Condition

The patients with suicidal ideation who are randomly assigned to the TAU+ condition receive an additional intervention called Future Oriented Group Training. There are 4 to 8 participants in each group, and the sessions are led by one trainer. This intervention consists of three major elements: the training sessions, the workbook with a accompanying audio cd, and a website.

The main goal of this training is to decrease suicidal thinking by stimulating realistic future thinking and reducing hopelessness. The training promotes goal directed and future oriented behavior by combining cognitive therapy, problem solving therapy, and future thinking. This means that participants and trainers almost exclusively address things to come.

The 10 weekly group training sessions last one and a half hours each. They are organized as workshops. Participants listen to the trainer who explains and discusses relevant topics. The trainer asks for personal experiences, but remains on a practical and educational level. The trainer discusses general tendencies, and individual experiences are generalized and reformulated in terms of future oriented cognitions and behavior. How would this kind of thinking, or that way of behaving, influence one's chance of reaching future positive goals? And what can be done about this?

The exercises and texts included in the workbook promote realistic thinking and help participants to create a personal meaningful future, by accomplishing goals that make life worthwhile again. In the workbook notorious cognitive patterns among suicidal patients are challenged, like dichotomous thinking and external locus of control. The participants receive information about suicidal vulnerability and factors influencing this vulnerability, for instance perfectionism, social isolation, and alcohol and drug abuse. The workbook discusses several practical steps, like making a survival plan, and creating a scrapbook with positive elements from their present and their past, in order to find strength when they feel hopeless. The workbook comes with an audio cd, with additional exercises that are in line with the contents of the workbook.

The supplementary website provides information about the training and the research project. It gives directions about the practical steps participants can take, like where to find help for their alcohol problems. It also provides means to discuss the training and exchange information. The website hosts a message board.

Further information about the training can be found in the summary of the workbook (Additional file 1).

### Treatment integrity

The trainers are instructed by two of the authors ([name] and AK). The training is structured along a treatment-manual and each session is being audio-taped and analyzed by one of the authors ([name]). The trainers fill in a form which states the main topics for each session in order to help them to stay focused on the manual.

### Control Condition

Participants in the control condition receive treatment as usual. Our training is additional and does not interfere with the ongoing treatment. In order to be able to compare the TAU and the TAU+ group we gather information on several characteristics of treatment as usual.

### Measurements

#### Sample characteristics

We gather information about demographic characteristics (age, marital status, education level) and parasuicidal behavior (self harming, past suicide attempts, risky behavior in traffic) and drug and alcohol abuse.

### Primary Outcome

#### Suicide ideation

With the Scale for Suicide Ideation [40] (SSI) we assess the presence and the level of suicide ideations. The SSI is a 19-item, clinician-administered semi structured interview which has demonstrated high reliability, with an internal-consistency coefficient (Cronbach's alpha) of 0.89, and a reported interrater reliability coefficient of 0.83.

### Secondary Outcomes

#### Depression

The Beck Depression Inventory BDI-II [41] is a self-administered 21 item self-report scale measuring supposed manifestations of depression. The BDI-II takes approximately 10 minutes to complete. Internal consistency for the BDI-II ranges from .73 to .92 with a mean of .86 [42]. The BDI-II has a split-half reliability co-efficient of .93.

